## Abstract

**Background:**

Pulmonary arterial hypertension is a rare disorder associated with poor survival. Endothelial dysfunction plays a central role in the pathogenesis and progression of pulmonary arterial hypertension. Inflammation appears to drive this dysfunctional endothelial phenotype, propagating cycles of injury and repair in genetically susceptible patients with idiopathic and disease-associated pulmonary arterial hypertension. Therapy targeting pulmonary vascular inflammation to interrupt cycles of injury and repair and thereby delay or prevent right ventricular failure and death has not been tested. Spironolactone, a mineralocorticoid and androgen receptor antagonist, has been shown to improve endothelial function and reduce inflammation. Current management of patients with pulmonary arterial hypertension and symptoms of right heart failure includes use of mineralocorticoid receptor antagonists for their diuretic and natriuretic effects. We hypothesize that initiating spironolactone therapy at an earlier stage of disease in patients with pulmonary arterial hypertension could provide additional benefits through anti-inflammatory effects and improvements in pulmonary vascular function.

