MR antagonists have been widely used in patients with left-sided heart failure or left ventricular (LV) dysfunction post-myocardial infarction [15,16]. The clinical benefit of MR antagonists in these patients has been linked to poorly characterized anti-inflammatory properties and less so to their better understood diuretic or natriuretic effects [17,18]. Spironolactone, a combined MR and androgen receptor antagonist, improves endothelial dysfunction in patients with left-sided heart failure [19-21], rheumatoid arthritis [22], and in women with polycystic ovarian syndrome [23], suggesting a possible mechanism for its clinical efficacy in these patient populations. One group has suggested that spironolactone interferes with NFκB signaling in human monocytes in a non-MR dependent manner, but the molecular basis for this conclusion has not been further clarified [24,25]. In a recent study utilizing two different animal models of PH, MR antagonists demonstrated beneficial effects on aldosterone-induced pulmonary vascular remodeling, RV hypertrophy and oxidant stress [26]. Current management of patients with severe PAH and New York Heart Association/World Health Organization (NYHA/WHO) class IV symptoms includes use of MR antagonists once clinical right heart failure has developed for their diuretic and natriuretic effects [27]. Initiating therapy with spironolactone at an earlier stage of disease in patients with PAH is a novel approach to treatment and could provide benefits through anti-inflammatory mechanisms and improvements in endothelial function that might alter the natural history of PAH. To date, however, there have been no randomized clinical trials examining the safety and efficacy of MR antagonist therapy in PAH without right heart failure. *In vitro* data from our laboratory demonstrate that spironolactone suppresses NFκB-mediated inflammatory signaling in human endothelial cells (unpublished results). We are actively investigating the molecular mechanisms that mediate the anti-inflammatory activity of spironolactone and the relative contributions of MR, androgen receptor and progesterone receptor, as well as NR-independent effects.

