b. Echocardiographic evidence of severe RV dysfunction

AND

c. Clinical signs which may include, but are not limited to elevated jugular venous pressure, ascites, and lower extremity edema

2. Patients with WHO Group 1 PH and a prior diagnosis of cirrhosis with portal hypertension as evidenced by a history of ascites, hepatic encephalopathy and/or varices prior to enrollment.

3. Patients with WHO Group 1 PH and evidence of active infection. (Patients with HIV infection and two consecutive viral loads of <500 on their most recent determinations in the past 12 months will be considered to have inactive infection.)

4. Patients with WHO Group 1 PH who have taken spironolactone or eplerenone within the last 30 days.

5. Known or suspected allergy to spironolactone.

6. Pregnant or breastfeeding women.

7. Age <18 years.

8. Inability to provide informed written consent for participation in the study.

9. Chronic kidney disease defined as estimated glomerular filtration rate (eGFR) of <50 mL/min/1.73 m^2^ of body surface area. (eGFR will be calculated using the isotope dilution mass spectrometry-traceable Modification of Diet in Renal Disease Study equation and corrected for body surface area as follows: eGFR = 175 × (serum creatinine in mg/dL)^-1.154^ × (age in years)^-0.203^ × [1.212 if African-American] × [0.742 if female].)

10.  Serum potassium at the time of enrollment of >5 mEq/L or current use of potassium-sparing diuretics, angiotensin-converting enzyme (ACE) inhibitors, angiotensin II receptor blockers or drospirenone-containing oral contraceptives.

All participants will undergo baseline testing under our Natural History protocol and serial (12 and 24 weeks) testing under this protocol according to the schedules outlined in Additional file 1: Figure S1 (all time points are approximations, ±7 days). Following each interval assessment period (baseline, 12 and 24 weeks), patients will be discharged home under the care of their referring and/or primary physicians. During the study, participants are permitted to have other medications, including PAH-specific therapies, adjusted by their primary physician as clinically necessary.

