### Study endpoints

Our primary endpoint is the effect of spironolactone therapy on the change in placebo-corrected 6-minute walk distance at 24 weeks relative to baseline values and the incidence of clinical worsening in the spironolactone group compared to placebo. Clinical worsening will be defined as the addition of a new PAH-specific medication (a prostacyclin, an endothelin-1 receptor antagonist or a phosphodiesterase-5 inhibitor), dose or route escalation (that is inhaled prostacyclin changed to intravenous prostacyclin) of a current PAH-specific medication, development of right heart failure requiring hospitalization or an escalation in outpatient diuretic therapy (that is, initiation of a new diuretic or a dose escalation of current diuretic therapy), transplantation, or death.

Secondary endpoints include effect of spironolactone therapy on exercise capacity, as measured by the change in placebo-corrected VO_2_ maximum at 24 weeks relative to baseline values; effect of spironolactone therapy on plasma markers of vascular inflammation (see Table 2) and peripheral blood mononuclear cell (PBMC) gene expression profiles, comparing changes from baseline between the treatment and placebo groups; effect of spironolactone therapy on sympathetic nervous system activation, renin-angiotensin-aldosterone system activation and sex hormone metabolism, comparing changes from baseline between the treatment and control groups (see Table 2); effect of spironolactone therapy on RV function as assessed by echocardiography, magnetic resonance imaging (MRI) and N-terminal pro-brain natriuretic peptide (NT-proBNP), comparing changes from baseline between the treatment and placebo groups; and safety and tolerability of spironolactone therapy as determined by the rate of study drug discontinuation due to hyperkalemia (serum potassium ≥5.3 mEq/L), renal insufficiency (serum creatinine rise >50% of baseline), or other side effects such as breast pain and gynecomastia compared to placebo.

**Table 2 T2:** Biomarker assessment

**Markers of endothelial dysfunction**	**Neurohormonal axis**
**Adhesion molecules**	**Sympathetic activation**
sICAM-1, sVCAM-1, sE-selectin	Epinephrine, norepinephrine, arginine vasopressin
**Markers of activated coagulation**	**Renin-angiotensin-aldosterone system activation**
von Willebrand factor, thrombomodulin, sP-selectin	Renin activity, aldosterone, angiotensin II, NT-proBNP
**Cytokines and chemokines**	**Sex hormone metabolism**

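### A difference in clinical worsening could partly reflect diuretic substitution: the composite counts diuretic escalation, and the study drug's class is used in PAH for its diuretic effect

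*Protocol article*

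**What the plan says.** Under Study endpoints, the primary endpoint joins the change in 6-minute walk distance with "the incidence of clinical worsening in the spironolactone group compared to placebo". The list of worsening events includes "development of right heart failure requiring hospitalization or an escalation in outpatient diuretic therapy", and a parenthesis explains the escalation as "initiation of a new diuretic or a dose escalation of current diuretic therapy". No amount, clinical sign or adjudication is given for it.

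Under Nuclear receptors and inflammation, current management of severe PAH "includes use of MR antagonists once clinical right heart failure has developed for their diuretic and natriuretic effects". The abstract likewise refers to "use of mineralocorticoid receptor antagonists for their diuretic and natriuretic effects". It then states the hypothesis that earlier spironolactone "could provide additional benefits through anti-inflammatory effects and improvements in pulmonary vascular function".

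Under Overview of study design and study population, the exclusion that concerns diuretics is "current use of potassium-sparing diuretics, angiotensin-converting enzyme (ACE) inhibitors, angiotensin II receptor blockers or drospirenone-containing oral contraceptives", so other diuretics may be in use at entry. The four-week stability requirement covers PAH-specific therapy and functional class, not diuretics. During the trial "participants are permitted to have other medications, including PAH-specific therapies, adjusted by their primary physician as clinically necessary".

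Under Study analysis, time to clinical worsening is shown by Kaplan-Meier curves and compared by a log-rank test on the whole composite. The article does not discuss the overlap between this component and the drug's own action.

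**The concern.** A placebo participant who retains fluid may be given a new or larger diuretic and so have an event. A spironolactone participant with the same tendency already takes, as blinded study drug, an agent of a class used for that purpose, so the need may be smaller or may not show. The component then responds to the drug's known action as well as to any slowing of disease.

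The hypothesis is a benefit additional to the diuretic one. If fewer diuretic changes drove a favorable composite, it could be reported as delayed worsening in support of that hypothesis, and the log-rank result alone would not show the difference. Blinding does not help, because the cause is pharmacology and not knowledge of the assignment.

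The clause can also be read in two ways, and the event count depends on which is used.

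**Working it through.** **The plan's own figure.** The only power statement concerns walk distance: at least 84% for an effect size of 0.9 at two-sided 0.05, with at least 50 completers at 1:1. With 25 per arm, 0.9 × √(25/2) = 3.18, and Φ(3.18 − 1.96) = 88.9%; the exact t-test gives 87.7%. The statement stands. The article gives no event rate, component share or power for clinical worsening, so what follows is illustration.

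**The two readings of the clause.**
- Reading A: any outpatient diuretic initiation or dose increase is an event by itself.
- Reading B: the event is right heart failure that requires either hospitalization or diuretic escalation. The commas separate the other items and none precedes the second half of this one, so B is the more natural reading.

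The overlap remains under B. Individual participant stopping rules, item 1, identifies right heart failure by signs such as raised jugular venous pressure, ascites and edema. A diuretic can suppress these.

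**Illustrative size.** Assume proportional hazards and no drug effect on any other component. Let P be the 24-week placebo risk of the composite, s the share of placebo events that are diuretic-only, and r the proportional reduction of those events by the drug.
- Composite hazard ratio: HR = 1 − s × r.
- Spironolactone risk: 1 − (1 − P)^HR.
- Expected events with n per arm: E = n × (P + spironolactone risk).
- Chance of a significant log-rank result favoring spironolactone (Schoenfeld approximation): Φ(√(E/4) × |ln HR| − 1.96). This is 2.5% when HR = 1.

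All ranges are assumed: P 20–40%, s 30–70%, r 30–80%.

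| P | s | r | HR | Spironolactone risk | Chance, 25 per arm | Chance, 35 per arm |
|---|---|---|---|---|---|---|
| 20% | 30% | 30% | 0.91 | 18.4% | 3.5% | 3.7% |
| 30% | 50% | 50% | 0.75 | 23.5% | 7.6% | 9.0% |
| 40% | 70% | 80% | 0.44 | 20.1% | 35.6% | 46.9% |

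Middle row in full: HR = 1 − 0.5 × 0.5 = 0.75; risk = 1 − 0.70^0.75 = 23.5%; E = 25 × (0.300 + 0.235) = 13.4; √(13.4/4) × 0.288 = 0.53; Φ(0.53 − 1.96) = 7.6%.

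**Second parametrization.** Treat diuretic and other events as independent, with other events equal in both arms, and take HR as the ratio of the logs of the event-free proportions.
- Diuretic events 10% placebo v 5% spironolactone, other events 15%: ln(0.95 × 0.85)/ln(0.90 × 0.85) = 0.80.
- 15% v 7.5%, other 10%: ln(0.8325)/ln(0.765) = 0.68.
- 20% v 5%, other 10%: ln(0.855)/ln(0.72) = 0.48.

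The direction is the same throughout. The size depends entirely on the assumptions, and with about 7 to 27 events over the whole grid the log-rank approximation is rough.

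**The case against.** The strongest case against the point has five parts.

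1. *The clause already ties escalation to right heart failure.* This largely stands. A reader might infer that any diuretic change is an event on its own, but the punctuation favors the narrower reading. That lowers the likely number of diuretic-only events without removing the overlap.

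2. *Component tables and sensitivity analyses belong in the SAP.* A separate plan may contain them, and their absence from an article would be no finding. The point rests on what the article does fix: an endpoint definition that overlaps the drug's action, with a clause open to two readings.

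3. *The objective is the effect of early treatment on clinical worsening, by whatever mechanism.* This is fair. Fewer episodes needing treatment may be a real benefit, walk distance is the powered endpoint, and mechanism has its own secondary endpoints. The background also says that in left-sided disease the benefit has been linked more to anti-inflammatory than to diuretic effects. So the inference that a positive composite would show only the known action of the drug is not supported. It would be ambiguous.

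4. *The magnitudes are assumed, in a population enrolled without clinical right ventricular failure.* This stands in full. In the middle case a significant result is still unlikely, and the trial calls itself a pilot.

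5. *Removing diuretic-only events does not give a clean answer.* This also stands. Participants with clinical right heart failure leave the protocol, so later events may go unseen, possibly to a different extent in each arm. A diuretic effect could also lower hospitalization for right heart failure, which stays in the reduced composite. A hazard ratio of 1.00 after the exclusion would hold only by assumption.

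**Conclusion.** The concern holds in a limited form. A difference in clinical worsening could partly reflect diuretic substitution and not the additional anti-inflammatory and vascular benefit that the trial hypothesizes. This follows from the endpoint list read beside the article's own account of the drug class, on either reading of the clause.

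The size cannot be derived from the document. Hazard ratios from 0.91 to 0.44, and a chance of a significant favorable result from 3.5% to 47% against 2.5%, rest on assumed risks, shares and reductions and on no other drug effect. The middle case is modest: HR 0.75 and 7.6% to 9.0%.

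A reader might infer that the composite is invalid, or that any gain on it would be pure substitution. The document supports neither. What is at risk is the attribution of a difference.

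**What to change.** Keep the composite as defined, and make these changes:

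- **Study endpoints:** reword the item so that the diuretic clause has one reading, stating whether escalation counts only when right heart failure has developed.
- **Study analysis:** beside the log-rank test, prespecify a supportive time-to-event analysis that does not count events consisting only of outpatient diuretic initiation or escalation. Add a table of first events by component and arm.
- **Follow-up:** continue to collect death, transplantation, hospitalization and PAH-therapy changes to week 24 after a diuretic-only event or removal under the individual stopping rules. If this is not done, state that the supportive analysis is cause-specific and subject to informative censoring.
- **Interpretation:** state in advance that a composite difference resting mainly on diuretic-only events will not be attributed to effects beyond diuresis. Requiring only that the supportive estimate point in the same direction would be too weak. With few events and no true effect on the remaining components, direction agrees about half the time.

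The trial was still recruiting when the article appeared, so this could be settled before unblinding. The cost is a clarified sentence, one analysis, one table and, where it is not already done, event follow-up after removal. The supportive analysis will have fewer events and less precision, and it cannot remove any diuretic effect on right-heart-failure hospitalization.

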#### Study analysis

Participant characteristics will be summarized using contingency tables (for categorical variables), means and standard deviations for continuous variables that are approximately normally distributed (transformed if needed) or median and inter-quartile range for continuous variables that are not normal.

For the primary endpoints, changes in 6-minute walk distance (24 weeks versus baseline) will be compared between the two groups using linear mixed models (LMMs), Kaplan-Meier curves will be plotted to show the time to clinical worsening, and a log-rank test will be used to compare the two arms. Chi-squared tests or Fisher exact tests, t-tests or Wilcoxon rank-sum tests will be used to compare variables between the two arms when appropriate. The rates of study drug discontinuation between the two arms will be compared using the Fisher exact test, and a logistic regression will be considered to account for potential confounders if the two arms are imbalanced. The causes of discontinuation will be tabulated and compared if appropriate.

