If while on therapy a patient’s serum potassium level increases to 5.3 to 5.9 mEq/L, the study drug will be stopped and their serum potassium level will be checked again within 24 to 48 hours (Figure 2). At the study investigators’ discretion, any participant with a potassium level ≥5.3 mEq/L can be referred for medical evaluation at the nearest health care facility. If the repeat serum potassium is <5.3 mEq/L, then the study drug will be resumed at the previous dose and serum potassium measurement will be repeated again 72 to 96 hours later, and then weekly for two weeks, followed by resumption of the normal monitoring schedule as long as the serum potassium remains <5.3 mEq/L. If the serum potassium remains ≥5.3 mEq/L on two consecutive blood draws, the study drug will be discontinued. Delay in laboratory monitoring longer than 48 hours from the specified time frame in participants with a serum potassium of ≥5.3 mEq/L will result in that patient being removed from the protocol. If at any time the serum potassium is ≥6.0 mEq/L (Figure 2), the study drug will be discontinued and the participant will be referred to the nearest health care facility where standard treatment for hyperkalemia can be provided. In these participants, the study drug will not be restarted and they will be removed from the protocol. If while on the study drug a participant’s serum creatinine increases >50% then the study drug will be discontinued and the participant will be removed from the protocol. Prior to initiation of the study drug and throughout the trial during follow-up visits, participants will be asked about the presence of breast pain and, in male participants, the development of gynecomastia.

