### Risks and discomforts

#### Risks associated with spironolactone therapy

The most significant risks associated with spironolactone therapy include hyperkalemia, renal insufficiency, hypovolemia and gynecomastia with or without breast pain. In a large trial of patients with NYHA class III and IV LV heart failure (the mean dose of spironolactone was 26 mg and dose titration up to 50 mg daily), the incidence of severe hyperkalemia (>6 mEq/L) was not significantly different between the spironolactone treatment group (2%) and placebo (1%) but the median potassium concentration did increase by 0.30 mmol/L in the spironolactone-treated group [15]. The median creatinine concentration also increased (0.05 to 0.10 mg/dL) in the spironolactone-treated group. The risk of hyperkalemia while on spironolactone therapy is increased in the presence of renal insufficiency, concurrent use of ACE inhibitors or angiotensin receptor blockers, potassium-sparing diuretics or NSAIDs [66]. Precautions that will be taken include: participants will be counseled to avoid foods high in potassium and to avoid concurrent use of NSAIDs; patients taking ACE inhibitors, angiotensin receptor blockers, or potassium-sparing diuretics will be excluded from the study; participants will undergo frequent monitoring of serum potassium, creatinine and blood urea nitrogen; cessation of the study drug when serum potassium ≥6 mEq/L or when it remains ≥5.3 mEq/L on two occasions; and cessation of the study drug when creatinine increases by >50% of baseline value.

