Gynecomastia in men and painful breast enlargement in women may occur in participants treated with spironolactone and appear to be related to dose and duration of therapy [67-69]. The Randomized Aldactone Evaluation Study reported incidences of gynecomastia and breast pain in 9% and 2% of spironolactone-treated patients, respectively. This was significantly different from placebo and led to discontinuation of the study drug in 2% of spironolactone-treated patients in this trial [15]. In the majority of cases, gynecomastia and breast pain subside with cessation of the drug [68,70]. Prior to initiation of the study drug and throughout the trial during follow-up visits, participants will be asked about the presence of breast pain and, in male patients, the development of gynecomastia. If while on the study drug a participant develops significant breast pain or gynecomastia then the study drug will be discontinued. Additional side effects reported with spironolactone therapy and related to its progesteronal and anti-androgenic activity include menstrual irregularities (amenorrhea, postmenopausal bleeding), decreased libido and erectile dysfunction [67-69]. These also appear to be dose related and typically resolve upon drug cessation [69,71].

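### The safety endpoint and its only named analysis count drug discontinuations, which is narrower than the stated safety aim and misses a single potassium of 5.3 to 5.9 that settles on recheck

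*Protocol article*

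**What the plan says.** Study endpoints gives the safety endpoint as "safety and tolerability of spironolactone therapy as determined by the rate of study drug discontinuation due to hyperkalemia (serum potassium ≥5.3 mEq/L"), a creatinine rise of more than 50%, or other side effects, compared with placebo. Study analysis follows it: "The rates of study drug discontinuation between the two arms will be compared using the Fisher exact test", with logistic regression if the arms are imbalanced. It adds that "The causes of discontinuation will be tabulated and compared if appropriate".

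The Abstract and the Objectives describe safety more widely. The Abstract names monitoring for hyperkalemia and renal insufficiency in addition to discontinuation. The Objectives list both conditions beside study drug intolerance, relative to placebo.

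The section Spironolactone treatment sets the rule for a potassium of 5.3 to 5.9 mEq/L: "the study drug will be stopped and their serum potassium level will be checked again within 24 to 48 hours". It continues: "If the repeat serum potassium is <5.3 mEq/L, then the study drug will be resumed at the previous dose". Discontinuation follows if potassium is ≥5.3 on two consecutive draws, or at any value ≥6.0. Item 3 of Individual participant stopping rules words this differently: more than one episode ≥5.3, which it labels serious hyperkalemia, or one episode ≥6.0.

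Potassium, blood urea nitrogen and creatinine are drawn on day 7 and at weeks 6, 9, 12, 16, 20 and 24. On expected effects, the risk section reports from a large left-heart-failure trial that "the median potassium concentration did increase by 0.30 mmol/L in the spironolactone-treated group", and that median creatinine rose by 0.05 to 0.10 mg/dL.

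**The concern.** Discontinuation is a management decision that follows a harm, and here a rule stands between the two. The first potassium is drawn on drug and the recheck 24 to 48 hours later off drug, so the recheck tends to remove episodes that the drug itself caused. A participant can therefore reach the level that the endpoint names, and that the stopping rules call serious, without being an endpoint event.

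The endpoint also turns a continuous laboratory signal into an uncommon yes/no event. The article says no randomized trial has examined this drug class in pulmonary arterial hypertension without right heart failure, and safety is a stated aim. A report limited to the defined endpoint could show similar discontinuation in both arms while more participants on spironolactone reached 5.3 mEq/L, or while potassium was clearly shifted.

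**Working it through.** **1. Which outcomes reach the endpoint**

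The article gives no figure for the safety endpoint, so there is none to reproduce. The check is to trace each outcome through the rules in Spironolactone treatment and Individual participant stopping rules.

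| Outcome on study drug | Action in the protocol | Endpoint event? |
|---|---|---|
| One potassium of 5.3 to 5.9, recheck below 5.3 | Drug resumed | No |
| Potassium ≥5.3 on two consecutive draws | Discontinued | Yes |
| A second, separate episode ≥5.3 | Discontinued (stopping rule 3) | Yes |
| Any potassium ≥6.0 | Discontinued | Yes |
| Potassium shift that stays below 5.3 | None | No |
| Creatinine rise >50% | Discontinued | Yes |
| Creatinine rise of 50% or less | None | No |
| Significant breast pain or gynecomastia | Discontinued (stopping rule 7) | Yes |

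Three rows are missed: the single settled episode and the two kinds of sub-threshold shift. The settled episode meets the ≥5.3 figure in the endpoint. The third row is counted only through stopping rule 3, because the text in Spironolactone treatment speaks of consecutive draws.

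**2. Data against named analyses**

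The on-treatment laboratory time points are day 7 and weeks 6, 9, 12, 16, 20 and 24, which makes seven. Study analysis gives linear mixed models to oxygen consumption, plasma markers, hormones and right ventricular function. It names none for potassium or creatinine.

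**3. What the choice could cost (illustration only)**

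*Inputs from the document:* up to 70 enrolled and at least 50 completed, allocated 1:1, so 35 or 25 per arm; two-sided 5% level; potassium shift 0.30 mmol/L; severe hyperkalemia (>6 mEq/L) 2% vs 1% in the cited trial. *Assumed, not in the document:* every other event rate, the share that settles on recheck, and the standard deviation (SD) of potassium.

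Fisher exact power is the sum, over all pairs of counts with p ≤ 0.05, of the product of the two binomial probabilities. With 35 per arm:

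| Rates | Power |
|---|---|
| 2% vs 1% (cited, potassium >6 only) | about 0% |
| 10% vs 2% (assumed) | 7% |
| 15% vs 3% (assumed) | 22% |
| 7.5% vs 1.5% (the line above if half settle, assumed) | 3% |

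With no placebo events, 5 vs 0 gives p = 0.054 and 6 vs 0 gives p = 0.025.

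For a between-arm difference of 0.30 in mean potassium, power comes from the two-sample t-test with noncentrality (0.30/SD) × √(n/2):

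| Assumed SD | 25 per arm | 35 per arm |
|---|---|---|
| 0.35 | 84% | 94% |
| 0.40 | 74% | 87% |
| 0.50 | 55% | 70% |
| 0.60 | 41% | 54% |

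At SD 0.40 and 35 per arm, the 95% confidence half-width is t × SD × √(2/n) = 1.995 × 0.40 × √(2/35) = 0.19 mmol/L. Under these assumptions the laboratory values carry more information about the known effect than the discontinuation count does.

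**The case against.** The strongest reply is that this is a condensed article. Laboratory summaries commonly sit in the full protocol or analysis plan, neither of which is shown, and Study analysis has a general provision: "Chi-squared tests or Fisher exact tests, t-tests or Wilcoxon rank-sum tests will be used to compare variables between the two arms when appropriate". Protocol stopping rules has serious events, with severe hyperkalemia and renal insufficiency as examples, followed by treatment group. The monitoring board reviews data every six months, and related adverse events are reported. A reader might infer that settled hyperkalemia and laboratory shifts will go unreported. The documents do not support that reading, and the absence of laboratory tables is not itself a fault.

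This does not remove the narrower point. The endpoint is positively fixed as a discontinuation rate, and an analysis plan would normally carry out that definition. The general sentence names no safety variable. Severe hyperkalemia is defined as ≥6.0, so that example does not cover 5.3 to 5.9. Board review is oversight, and adverse event reporting depends on a judgment of relatedness.

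Other parts of the objection stand in full:

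- The cited trial's gynecomastia figures (9% affected, but side effects that "led to discontinuation of the study drug in 2% of spironolactone-treated patients in this trial") might seem to show the same undercount. They do not transfer, because this protocol requires discontinuation for significant breast pain or gynecomastia.
- The 2% vs 1% rates cover one component, in another population. They do not give the power of the planned test on all discontinuations.
- The 0.30 is a median increase in the spironolactone group, used above as a difference in means.
- Low power for rare events is expected in a pilot and would also affect a count of potassium ≥5.3 (22% in the illustration). The added counts are worth having as estimates.

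**Conclusion.** The point holds in limited form. The safety endpoint and its one named analysis are narrower than the safety aim in the Abstract and Objectives. The ≥5.3 mEq/L in the endpoint does not match the rules that decide discontinuation. What escapes is a single potassium of 5.3 to 5.9 that settles on recheck, together with potassium and creatinine shifts below the stopping thresholds. The more serious or repeated events are captured.

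This conclusion rests on the text alone. How many participants would be missed cannot be derived from the document, and the power figures only illustrate direction under assumed rates and SDs. A reader might go further and conclude that the main known harm will be understated in the results. That would require knowing that nothing beyond the endpoint is reported, which the article does not say. No view is taken on which potassium threshold or stopping rule is right.

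**What to change.** Reconcile the safety wording across the Abstract, Objectives, Study endpoints, Study analysis, Spironolactone treatment and Individual participant stopping rules. In particular, state how the ≥5.3 in the endpoint relates to the recheck rule, and how the consecutive-draw wording relates to the more-than-one-episode wording.

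Keep discontinuation and its causes as the tolerability measure. Add two analyses by arm, in all who took study drug:

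1. The number and percentage with any on-treatment potassium ≥5.3 and ≥6.0 mEq/L (the protocol's own thresholds), whether or not drug was stopped, with exact confidence intervals for the difference.
2. The between-arm difference in potassium and creatinine change at each scheduled visit, from the mixed model already planned for the biomarkers, adjusted for baseline, with 95% confidence intervals.

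The cost is a few sentences and a few tables. No visit, sample, monitoring step or stopping rule changes. The small downside is more safety comparisons, which should be presented as estimates and not as formal tests.
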